## Abstract

**Background:**

There is sufficient evidence that psychosocial stimulation (PS) benefits children’s neurocognitive behavior, however, there is no information on how it works when delivered through an Unconditional Cash Transfer (UCT) platform for poor rural population in developing countries. The objective of this study is to measure effects of adding PS for children of lactating mothers enrolled to receive UCT with health education (HE) on neurocognitive behavior of children in rural Bangladesh.

**Methods:**

The study will be conducted at 11 unions of Ullapara sub-district in Bangladesh. The study is a cluster randomized controlled trial with three-arms; (i) PS and UCT with HE (ii) UCT with HE and iii) Comparison arm. The cluster will be considered as an old *Ward* of a *Union*, the lowest tier of local government system in rural Bangladesh. There are three old *Wards* in a *union*. These three clusters will be randomized to one of the three arms. Similarly, randomization will be done for each 11 Unions and then 11 clusters will be assigned to an arm. Eighteen participants will be recruited from each cluster randomly (*n* = 196 in each arm). The intervention designed for one year includes UCT with HE for the poor as a safety net program in rural Bangladesh with or without PS. An age-based curriculum of PS is already available for Bangladeshi children and this will be administered by trained local women; play leaders (PL) in intervention clusters. The government of Bangladesh is providing UCT of taka 500 ($6.25) as maternity allowance per month with HE. The primary outcomes will be cognitive, motor and language composite scores measured by Bayley-III and behavior using Wolke’s behavior rating scale. The secondary outcomes will be children and mothers’ growth, family food security status, health seeking behavior, mothers’ depressive symptoms and self-esteem and violence against mothers.

**Discussion:**

The study will provide a unique opportunity to assess an integrated early childhood development intervention using UCT platform to mitigate developmental delays in poor vulnerable children of rural Bangladesh.

**Trial registration number:**

ClinicalTrials.gov NCT03281980, registered on September 13, 2017.

## Background

An estimated 250 million children below 5 years in low and middle income countries do not reach their maximum potential because of poverty and other risk factors e.g. malnutrition, stimulation, postpartum depression etc. [1]. Sometimes poor people become poorer due to catastrophic expenditure on health care and fall into the vicious cycle of poverty [2]. Social safety net program is a way of achieving wellbeing for the vulnerable. Conditional and unconditional cash transfer to the poor mothers has proved a way of reducing poverty and improving health outcomes for mothers and children worldwide [3–6]. Conditional cash transfer (CCT) alone was also found significantly effective for child development e.g. Oportunidades/Progresa program in Mexico [6]. On the other hand, studies reported that unconditional cash transfer (UCT) improved health outcomes [7] and nutrition [8]. The latest Lancet series on child development documented social safety net programs e.g. conditional and unconditional cash transfer, a suitable means for improving children’s development [9]. There is little information about effect of UCT alone on children’s development. Psychosocial stimulation alone and along with other health and nutrition programs was found to be effective for children’s cognition and behavior [10–14].

Ministry of Women and Children Affairs (MOWCA), Government of Bangladesh (GOB) provides maternity allowance for rural poor mothers; an unconditional cash transfer under safety net program of GOB. The mothers also receive limited health education (HE) program. The overall objective of the cash and health education (UCT-HE) training program is to ensure safety net in terms of morbidity, mortality and welfare during pregnancy and lactation period for both mother and child. Adding psychosocial stimulation to the program is proven to benefit children’s cognition, behavior and nutritional status. On the other hand the interventions together will address mothers’ physical and mental health and self-esteem and family’s food security because receiving extra cash as well as education on health and psychosocial stimulation will enhance mothers’ capacity in many aspects.

But little is known about the effects of psychosocial stimulation and UCT with HE program on children’s cognition and behavior.

## Methods

### Research objectives

The primary objective of this study is to measure the effects of adding psychosocial stimulation to an UCT-HE program on cognitive, language and motor development and behavior of young children. The secondary objectives are to measure effects of the programs on:Children’s growthMothers’ nutritional status, mental health (depression symptoms), self-esteem and exposure to domestic violenceHousehold food security status, health seeking behavior and health care expenditureTo evaluate cost effectiveness of the intervention

### Hypothesis

Our primary hypotheses are: 1) UCT-HE program will improve children’s cognitive, motor and language development and behavior compared to comparison group; 2) Adding psychosocial stimulation to UCT-HE program will have an additive effect on children’s cognitive, motor and language development and behavior compared to the UCT-HE group.

Our secondary hypotheses are that additionally the intervention will: 1) improve children and mothers’ nutritional status; 2) reduce mothers’ depressive symptoms and improve their self-esteem and reduce exposure to domestic violence; 3) improve household food security status, health seeking behavior and health care expenditure and 4) be cost effective.

### Study area

The study area is Ullapara, Sirajgonj, a sub-district of rural Bangladesh. There are 14 *Unions* in this sub-district. Like many other sub-districts risk factors for poor development e.g. poverty, malnutrition and unstimulating home environment, are all prevalent in the study area. Rural areas are much alike in terms of demography, topography, economy and health system in Bangladesh.

### Study design

This is a cluster randomized controlled trial with three arms: i) Psychosocial stimulation and UCT-HE ii) UCT-HE and iii) Comparison arms. The comparison arm will consist of those who are eligible to receive UCT but do not receive it due to resource constraints of the government.

### Sample size

The sample size is estimated based on an effect size of 0.45 SD and considering 80% power, 5% level of significance, and intraclass correlation (ICC) of 0.05 and an attrition rate of 25%.. In our previous studies of psychosocial stimulation alone, we have achieved an effect size of 0.52 SD on children’s development [15], but here we use effect size of 0.45 SD to be conservative. The study therefore requires 594 mother-child dyads in 33 clusters with 18 participants in each cluster.

### Intervention

The intervention includes:i)Psychosocial stimulation andii)UCT (Maternity allowance) with HE awareness program

Psychosocial stimulation: The participants will receive fortnightly sessions of psychosocial stimulation at home by community female play leaders for one year. The play leaders will be selected from the same locality and will be trained on the curriculum of psychosocial stimulation for 2 weeks. They will visit children’s homes carrying home-made toys and picture books and will demonstrate play activities to the mothers. The toys will be left in the homes at each visit and exchanged with new toys on the following visit. The play leaders will also convey messages on language development and nutritional care for the children. The curriculum was first developed and used in Jamaica and then a culturally modified and translated version was developed for use in Bangladesh [16]. The curriculum is based on improving the mother-child interaction and providing developmentally appropriate activities for the child. The curriculum has already been used in Bangladesh by Child Development Unit of icddr,b and has shown significant benefits to children’s development [11–13, 15] and growth [12, 15].

Unconditional Cash Transfer (Maternity allowance) with Health education awareness program: MOWCA provides maternity allowance of taka 500 ($6.25) for each targeted poor pregnant mother under safety net program of the GOB. The mothers receive the cash every six months for two years through banking channel. The objectives of the allowance are to help improving mothers and children’s health and wellbeing. The eligibility criteria for getting UCT and HE are:

1) mother’s age is equal to or more than 20 years; 2) mother is pregnant during UCT enrolment 3) the mother has no child or one child; 4) monthly income of the mother is less than Taka 1500; 5) the family owns a residence only or lives in residence of others; 6) the mother or the family do not have agricultural land or pond for fish culture and 7) poor and disabled women will have priority to receive UCT .

All mothers in each *union* under the UCT (maternity allowance) program will receive training by designated local NGOs (LNGOs) or community based organizations (CBOs) through MOWCA, GOB funding. HE programme is designed to educate mothers on theirs and their children’s health and nutrition, women’s right and welfare in a broad way. The mothers are also motivated to spend the allowance for improving their and their child’s health and welfare. MOWCA developed and approved the curriculum for HE program, which the mothers are supposed to receive in 13 sessions over two years of the UCT program. The number of eligible mothers to receive UCT with HE is larger than those who receive it, because of resource constraints of GOB.

### Participants recruitment and randomization

Eleven *Unions* will be randomly selected out of 14 *Unions* from Ullapara, Sirajgonj sub-district in rural Bangladesh. A *Union* is the lowest tier of local government system in the country. Three old *Wards* together make a *Union*. On an average there are 10 thousand populations in an old *Ward*. Many administrative and resource allocation are done considering the old *Wards* as a small unit in the health system of Bangladesh. This old *Ward* will be considered as a cluster for the study. A restricted randomization process will be followed where each of the three clusters of a *Union* will be randomly allocated to one of the three arms. Therefore, 11 *Wards* will fall under each of the three arms.

The participants will be the recipients of UCT -HE program or those eligible for the program but not receiving it. Since the Government is providing UCT -HE to 79 mothers in each *Union,* the research team is expecting to get approximately 26 participants in each cluster. On an average18 participants will be recruited randomly in each cluster of the arm i) and ii).

We will collect a list to identify potential beneficiaries from the clusters of the comparison arm (arm iii) through survey following the eligibility criteria of the recipients for the UCT - HE program. Then we will exclude the recipients of the UCT -HE program from the list through discussion with local government authority of Ullapara sub district. Finally, we will enrol 18 participants randomly in each cluster of this arm (arm iii). We will not impede providing GOB program in the comparison clusters due to ethical consideration and it is a limitation for the study. Permission from the GOB official will be obtained to use the information about the participants. The recruitment and randomization process has been shown in the trial flow chart (Fig. 1).

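### Primary hypothesis 1 (UCT-HE versus comparison) is not protected by randomisation: ward allocation decides who is sampled, not who receives the cash

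*Protocol article*

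**What the plan says.** The Study design section presents a three-arm cluster randomised trial: stimulation plus UCT-HE (arm i), UCT-HE (arm ii) and comparison (arm iii). Under Participants recruitment and randomization, the three old wards of each union "will be randomly allocated to one of the three arms". The first primary hypothesis is that the "UCT-HE program will improve children’s cognitive, motor and language development and behavior compared to comparison group"; the second is that stimulation adds to UCT-HE.

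The cash is a government programme. The same recruitment section says: "Since the Government is providing UCT -HE to 79 mothers in each" union, from which the team expects about 26 recipients per ward. On comparison wards it says: "We will not impede providing GOB program in the comparison clusters due to ethical consideration and it is a limitation for the study".

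Under Inclusion criteria, arms i and ii require actual receipt of the government cash, and arm iii requires eligibility without receipt. The arm iii frame is a survey list of eligible women, after which "Then we will exclude the recipients of the UCT -HE program from the list". The Intervention section says that more mothers are eligible than receive the allowance, and its eligibility list ends with the rule that "poor and disabled women will have priority to receive UCT".

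The Data analysis section plans one intention-to-treat regression allowing for clustering, and says in general terms that confounders will be considered in all analyses.

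**The concern.** A cluster randomised trial supports a causal reading of a contrast when the random allocation decides which clusters get the treatment. Here it decides that for stimulation but not for cash. If arm ii versus arm iii is reported as a randomised primary result, one of the trial's two primary hypotheses will be read as the causal effect of UCT-HE when the design cannot separate that effect from how the government chose recipients. This applies to a positive, a null or a negative result, and a larger sample would not remove the problem. The same holds for arm i versus arm iii.

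**Working it through.** **Step 1: what allocation changes in a ward.**

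| Ward drawn as | Government UCT-HE in the ward | Stimulation | Women sampled |
|---|---|---|---|
| Arm i | continues | yes | recipients |
| Arm ii | continues | no | recipients |
| Arm iii | continues | no | eligible non-recipients |

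The government figure is per union, so the expected number of recipients is 79/3 = 26.3 per ward in every arm, comparison wards included.

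**Step 2: a test of the arm ii versus iii contrast.** Suppose the same eligible women were sampled in arm ii and arm iii wards. Their expected UCT exposure would be equal, because allocation does not alter it. The whole difference in exposure therefore comes from the arm-specific inclusion criteria, which select on receipt. Randomising wards balances wards; it does not make recipients in one ward exchangeable with non-recipients in another.

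**Step 3: is receipt as good as random among eligible women?** Not on the stated rule. Funding falls short of the number eligible, and the shortfall is allocated with priority to poor and disabled women. The Background section names poverty as a reason why children fall short of their potential, so the selection factor is related to the outcome.

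**Step 4: arm i versus arm ii.** Both arms sample recipients, under the same criterion, from wards randomised within the same unions. Allocation decides who gets stimulation. This contrast is protected.

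**Step 5: the sample size is not at fault.** Inputs from the Sample size section: 0.45 SD, 80% power, 5% level (two-sided assumed), ICC 0.05, 25% attrition, 18 per cluster.
- Per arm, unclustered: 2 × ((1.96 + 0.84)/0.45)² = 77.5, so 78.
- Design effect: 1 + 17 × 0.05 = 1.85, giving 78 × 1.85 = 144.3.
- Attrition: 144.3/0.75 = 192.4, so 193.
- Clusters: 193/18 = 10.7, so 11 per arm; 11 × 18 × 3 = 594, as stated.

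**Step 6: what a selection difference would do (assumed values only).** After attrition each arm has 11 wards × 13.5 = 148.5 children. The SE of a pairwise contrast is √[2 × (0.05/11 + 0.95/148.5)] = 0.148 SD. Assume that recipients are poorer by 0.2 to 0.5 SD on an index correlated 0.3 with the outcome, with no adjustment. The bias is then 0.3 × 0.2 = 0.06 to 0.3 × 0.5 = 0.15 SD against UCT, or 0.41 to 1.01 SE. With no true effect:
- chance of a significant result in favour of UCT: Φ(−1.96 − 0.41) = 0.9% to Φ(−1.96 − 1.01) = 0.15%, against a nominal 2.5%;
- chance of a significant result against UCT: Φ(−1.96 + 0.41) = 6% to Φ(−1.96 + 1.01) = 17%.

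The two-sided total of about 7% to 17% thus lies almost entirely on the harm side.

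**The case against.** The strongest reply is that the article is open about much of this. The Study design section defines arm iii as eligible women left out by government resource constraints, and the recruitment section calls continued provision in comparison wards a limitation. All arms share the same income, residence and land criteria, so selection acts within an already restricted, poor group. Confounders are to be considered in regression, baseline socioeconomic data are collected, and a covariate list is commonly left to the SAP. The stated primary objective, adding stimulation to UCT-HE, is unaffected.

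Most of that is fair, and it limits the point. The absence of a named covariate list is not a fault here, and the main contrast stands. But nowhere does the article say that arm ii versus iii is non-randomised. Resource constraints explain why some women miss out, not which women. Neither the limitation sentence nor a general reference to confounders turns a selected contrast into a randomised one, and an SAP could not change the allocation.

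Three stronger readings are tempting but not supported:
- **An inflated rate of false claims of benefit.** The 7% to 17% in Step 6 rests on a gap that no document gives. Under the one selection rule that is stated, it falls mostly in the harm direction, whereas the hypothesis is one of improvement.
- **Favouritism towards better-connected families**, which would bias the other way. The documents do not mention it.
- **Arm iii screened on post-birth circumstances.** The survey follows the recipients' criteria, which include pregnancy at UCT enrolment. Nothing says whether these are applied retrospectively, and all arms enter the study with a child aged 6–16 months.

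**Conclusion.** The point holds as a matter of design. Arm ii versus iii and arm i versus iii are comparisons of government-selected recipients with eligible non-recipients, and the article wrongly places the first of these under a randomised, intention-to-treat heading. Arm i versus arm ii is randomised and answers the stated primary objective.

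The size of the selection effect cannot be taken from the documents; Step 6 is a sensitivity illustration, not an estimate. Its direction is not certain either. The priority rule on its own would push the estimate towards no benefit, but the documents do not show that it is the only influence on receipt. The conclusion rests on two statements in the article: the programme runs unimpeded in comparison wards, and arms are defined by receipt.

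**What to change.** In the Hypothesis, Study design and Data analysis sections, and correspondingly in any SAP:

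- State that randomisation supports arm i versus arm ii only, and make that the confirmatory primary contrast.
- Label arm ii versus iii and arm i versus iii as non-randomised comparisons, and do not describe them as intention-to-treat or as randomised effects.
- Analyse these two with prespecified adjustment for baseline characteristics that vary within the eligible group: socioeconomic status, income, maternal age, parity and the baseline outcome score. Table 1 already schedules socioeconomic, income and developmental data; age and parity are eligibility items. Criteria that every arm must meet in the same way, such as having no agricultural land or fish pond, are constant and cannot serve as adjusters.

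One caution: recipients join UCT in pregnancy, and the study baseline comes when the child is 6–16 months old. Baseline scores and income may therefore already reflect the programme, so results with and without them should be shown.

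The cost is mainly wording and an adjustment model. The trial is listed as ongoing, so any characteristic not recorded at entry would have to be asked later. Hypothesis 1 loses its status as a randomised primary claim. Because income and parity are truncated by the eligibility criteria, adjustment may remove only part of the selection, and residual confounding must be acknowledged.

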**Fig. 1 Fig1:**
[figure not shown]
Flow chart of the cluster randomization controlled trial

### Eligibility criteria for the study

Participants will be assigned to the study only if they meet all of the inclusion criteria and none of the exclusion criteria.

### Inclusion criteria

Mothers with a child aged 6–16 monthsEligible to receive UCT.○ Psychosocial stimulation and UCT with HE arm: Receiving unconditional cash from government○ UCT with HE arm: Receiving unconditional cash from government○ Comparison arm: eligible to receive UCT but not under UCT program.Not expected to leave the study site for more than 2 monthsHas a legally acceptable representative capable of understanding the informed consent document and providing consent on the participant’s behalf.

### Exclusion criteria

Legal guardian unwilling or unable to provide written informed consent.Known congenital anomaly, developmental disorder or severe developmental delayIf the child cannot be tested due to physical or behavioral problemsChildren of multiple birth e.g. twin, triplets

Mothers’ anthropometry	WHO standard	Mothers’ height, weight and MUAC	Baseline and end line
Socioeconomic data	Pretested questionnaire	Socioeconomic background of the participants	Baseline and end line
Cost data	Pretested questionnaire	Direct and indirect cost	Last quarter of the study and at the end

Play leaders assigned for psychosocial stimulation will be trained on the curriculum for 2 weeks and will be monitored by the supervisors. Weekly trouble shooting meetings will be held, any serious problem will be discussed and measures will be taken to solve it. The play leaders will receive monthly one-day refresher training on psychosocial stimulation. The investigators with long experience in the field of public health research will ensure smooth running of project activities in every step.

### Data storage and record retention

The data will be password protected and only members of the study team and investigators will have access to the password. Only unidentified data will be stored on the database.

Data will be available to the principal investigator. Following the archival period, hard copies of the data will be destroyed according to local procedures.

### Data analysis

All questionnaires will be checked and cross checked and necessary corrections will be made before data entry. Pre-coded questionnaire will be used to minimize data coding errors. Data will be checked for normality before analysis. Appropriate measures will be taken if there are any abnormal distributions. Potential confounding variables and effect modifiers will be considered for all analyses.

Background information will be presented in tabular forms with number and percentage in the three groups. Differences between groups in socioeconomic and other background characteristics will be analyzed using t-test for continuous variables for two groups and ANOVA for three groups. Intention-to-treat analysis controlling for the clustering effect will be followed using multiple regression analysis.

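### The planned baseline t-tests and ANOVA ignore ward clustering, so a nominal 5% test could falsely flag imbalance in up to about 15% (t-test) or 20% (ANOVA) of null comparisons at the protocol's own ICC

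*Protocol article*

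**What the plan says.** The Data analysis section of the protocol article names the baseline method: "Differences between groups in socioeconomic and other background characteristics will be analyzed using t-test for continuous variables" when two groups are compared, and ANOVA when there are three. It mentions no allowance for clustering there. The next sentence deals with the effect analysis: "Intention-to-treat analysis controlling for the clustering effect will be followed using multiple regression analysis". That is the only place in the section where clustering appears. An earlier paragraph of the same section adds, without linking it to the baseline tests: "Potential confounding variables and effect modifiers will be considered for all analyses".

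Under Participants recruitment and randomization, the cluster is the old ward, and the three wards of each of 11 unions are allocated one to each arm. The Sample size section assumes an "intraclass correlation (ICC) of 0.05" and arrives at "594 mother-child dyads in 33 clusters with 18 participants in each cluster".

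**The concern.** The protocol allows for clustering when it sets the sample size and when it estimates effects, but not when it compares the arms at baseline. A t-test or one-way ANOVA on individual dyads treats the dyads in each arm as independent. If mothers in the same ward resemble one another more than mothers in different wards of the same union, the standard error of a difference between arms is too small, and chance differences reach p < 0.05 too often.

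The baseline table is where a reader judges whether the arms are comparable. That judgement matters more than usual here, because arm iii is recruited differently: its mothers are eligible non-recipients found by survey, whereas arms i and ii consist of recipients. A p-value from an understated standard error gives neither the size of an imbalance nor a sound view of whether chance could explain it.

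This is a method that the article fixes, not a detail left to a later document.

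**Working it through.** **Inputs.** From the Sample size section: "effect size of 0.45 SD and considering 80% power, 5% level of significance", ICC 0.05, attrition 25%, and 33 clusters of 18. From the recruitment section: 11 unions, with one ward of each union in each arm. Assumptions: the test is two-sided, and the ICC of 0.05 also applies to baseline variables. The protocol gives no ICC for any baseline variable.

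**Reproducing the plan's own figure.**
- Per arm without clustering: 2 × (1.96 + 0.84)² / 0.45², rounded up to 78.
- Design effect: 1 + (18 − 1) × 0.05 = 1.85, so 78 × 1.85 = 144.3.
- Attrition: 144.3 / 0.75 = 192.4, rounded up to 193 per arm.
- Whole wards of 18: 193 / 18 = 10.7, rounded up to 11, so 11 × 18 = 198 per arm and 594 in total.

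The stated 594 is reproduced exactly, and it rests on a design effect of 1.85.

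**True size of a test that ignores clustering, with all of it between wards within unions.** The variance of an arm mean is 1.85 times what the test assumes, so the standard error is too small by a factor of √1.85 = 1.36.
- t-test: 2 × [1 − Φ(1.96 / 1.36)] = 2 × [1 − Φ(1.441)] = 0.150 (simulated 15.2%).
- Three-arm ANOVA: P(χ² with 2 df > 5.99 / 1.85) = exp(−5.99 / (2 × 1.85)) = 0.198 (simulated 20.1%).

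**Allowing for the allocation within unions.** Variation between unions adds equally to all three arms and cancels from their differences. If a share s of the ICC lies between unions, the variance ratio becomes approximately V = (1 − ICC) + 18 × ICC × (1 − s). At ICC 0.05 this is 0.95 + 0.90 × (1 − s). Putting V in place of 1.85 in the two formulas gives the following rates; the simulation used 20,000 trials of 11 unions × 3 wards × 18 dyads.

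| Share of ICC between unions | V | t-test, formula | t-test, simulated | ANOVA, formula | ANOVA, simulated |
|---|---|---|---|---|---|
| 0 | 1.85 | 15.0% | 15.2% | 19.8% | 20.1% |
| 0.5 | 1.40 | 9.8% | 10.0% | 11.8% | 12.2% |
| 0.8 | 1.13 | 6.5% | 6.5% | 7.1% | 7.2% |
| 1.0 | 0.95 | 4.4% | 4.5% | 4.3% | 4.3% |

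**Range over the ICC, with no union component (formula, t-test / ANOVA).**
- ICC 0.01: 7.0% / 7.7%
- ICC 0.02: 9.0% / 10.7%
- ICC 0.10: 23.3% / 33.0%

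**Check on the remedy.** A paired t-test of two arms on ward means, paired within union, rejected in 4.8% to 5.3% of null trials in every scenario simulated.

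**The case against.** Four counter-arguments carry weight.

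1. **The size is conditional.** The ICC of 0.05 is a sample-size input, and one ward per arm in each union removes variation between unions. A reader might infer that false flags will run at three to four times the nominal rate. That is only the upper limit at ICC 0.05, reached when none of the clustering lies between unions. The documents do not say how clustering divides between ward and union. This stands.
2. **Harm to the primary analysis is not shown.** A reader might infer that faulty baseline p-values will decide which covariates enter the primary model. The sentence on confounders precedes the baseline tests and states no selection rule, and the effect regression controls for clustering. As written, neither the effect estimate nor its standard error depends on the baseline tests. This stands.
3. **Not every flag would be false.** The calculated rates assume that the arms share one distribution. Arm iii is a differently selected group, so some of its differences may be real. Even between arms i and ii, differential consent or enrolment could cause imbalance that is not chance if recruitment followed ward allocation. It would therefore be too strong to say that a baseline comparison answers no question. This stands, but it calls for a valid comparison and does not defend an invalid one.
4. **An article condenses, and the analysis plan may say more.** This does not rescue the text. The article names specific tests and states control for clustering for one analysis and not for the other. The argument does hold for a full list of prespecified covariates, which belongs in the analysis plan and whose absence is no fault here.

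**Conclusion.** The concern holds in a limited form. The baseline tests named in the Data analysis section do not respect the randomised unit, and their p-values will be too small wherever a baseline variable clusters by ward within union. At ICC 0.05 the false-flag rate for a nominal 5% test is at most about 15% for the t-test and 20% for the three-arm ANOVA. It is about 10% and 12% if half the clustering is between unions, and there is no inflation if all of it is. A higher ICC for socioeconomic variables would raise these figures, and a larger union component would lower them; the protocol gives neither quantity.

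The consequence is limited to the baseline p-values and to how imbalance between arms is read. The sample size and the clustering control in the effect regression are unaffected. The correction is worth making because a stated method is wrong for the design and changing it costs almost nothing.

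**What to change.** In the Data analysis section, replace the baseline t-tests and ANOVA with summaries by arm (mean and SD, or number and percentage) and standardised differences. These show the size of any imbalance, which is what a reader needs for the comparisons with arm iii. If tests are kept, specify ward-level or mixed-model comparisons that account for both ward and union. Add one sentence saying that baseline significance will not be used to choose covariates; the present text neither says that it will be nor rules it out.

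This is a change of wording only. Sample size and data collection are unchanged, and the only loss is the conventional column of baseline p-values.

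### Wards are randomised in triplets within Union, but the stated outcome analysis does not name Union; if Unions differ, a ward-clustered model without it is conservative and gives up some power

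*Protocol article*

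**What the plan says.** Under Participants recruitment and randomization, the protocol article defines the old Ward as the cluster and describes a restricted randomisation. The three clusters of each Union "will be randomly allocated to one of the three arms", which yields 11 wards per arm. Each Union therefore supplies one ward to every arm.

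Under Data analysis, the outcome model is given in one sentence: "Intention-to-treat analysis controlling for the clustering effect will be followed using multiple regression analysis". The same section says that possible confounders and effect modifiers will be considered, without listing them. Union is neither included nor ruled out, and the way clustering will be handled (random effect, robust variance or ward-level summary) is not stated.

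Under Sample size, the assumptions are an effect of 0.45 SD, "considering 80% power, 5% level of significance", and "intraclass correlation (ICC) of 0.05 and an attrition rate of 25"%. One ICC is used, and no credit is taken for blocking by Union.

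**The concern.** The analysis should follow the restriction placed on the randomisation. Because every Union contributes one ward to each arm, differences between Unions cancel from every arm contrast. A model that recognises only wards still counts those differences as error, so its standard error describes a less precise design than the one carried out.

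Confidence intervals would then be too wide and the test would reject less often than its nominal level. Part of the precision bought by the restriction would not show in the reported results. The open confounder clause is unlikely to repair this: Union is balanced across arms by design, so a search for confounders gives no reason to select it.

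**Working it through.** **Inputs.** From Sample size: effect 0.45 SD, power 80%, alpha 5% (taken as two-sided; not stated), ICC 0.05, attrition 25%, 18 per cluster. From Participants recruitment and randomization: 11 Unions, three wards each, 11 wards per arm. Assumed, because the documents do not give it: the share *s* of the ICC that lies between Unions, varied from 0 to 100%.

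**Step 1: the plan's own figure.**
- Individually randomised: 2 × (1.960 + 0.842)² / 0.45² = 77.5, so 78 per arm.
- Design effect: 1 + (18 − 1) × 0.05 = 1.85, and 78 × 1.85 = 144.3.
- Attrition: 144.3 / 0.75 = 192.4, so 193 per arm.
- Clusters: 192.4 / 18 = 10.7, so 11 per arm, which is 11 × 18 = 198 per arm and 594 in total.

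The stated 594 is reproduced.

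**Step 2: standard error of a two-arm contrast.** After attrition a ward has 18 × 0.75 = 13.5 dyads. On a total variance of 1, the within-ward part of a ward mean's variance is 0.95 / 13.5 = 0.0704.
- True SE (Union cancels): √[2 × ((1 − s) × 0.05 + 0.0704) / 11].
- SE that a model without Union estimates on average: √[2 × (0.05 + 0.0704) / 11] = 0.148, whatever *s* is.

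At s = 50% the true SE is √[2 × (0.025 + 0.0704) / 11] = 0.132, so the reported SE is 0.1479 / 0.1317 = 1.12 times too large. At s = 100% the ratio is 0.1479 / 0.1131 = 1.31.

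**Step 3: size and power.** Ward means were simulated (100,000 trials per scenario) and analysed in two ways, each with the residual variance pooled over three arms: without Union, 33 − 3 = 30 df; with Union as a block, (3 − 1) × (11 − 1) = 20 df.

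| Union share of ICC (assumed) | True SE | SE ratio without Union | Size without / with Union | Power at 0.45 SD without / with Union |
|---|---|---|---|---|
| 0% | 0.148 | 1.00 | 4.9% / 5.0% | 83.7% / 82.4% |
| 25% | 0.140 | 1.06 | 3.8% / 5.0% | 84.8% / 86.3% |
| 50% | 0.132 | 1.12 | 3.0% / 5.1% | 86.3% / 90.1% |
| 75% | 0.123 | 1.21 | 2.1% / 4.9% | 87.8% / 93.8% |
| 100% | 0.113 | 1.31 | 1.3% / 5.0% | 89.3% / 96.6% |

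The 4.9% in the first row is 5% within simulation error. Power without Union also rises with *s*, because the contrast itself becomes more precise; only its estimated standard error does not follow.

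**The case against.** The strongest reply is that this is a condensed article and the analysis plan is not shown. Block terms and degrees-of-freedom methods are often left to that plan, and nothing in Data analysis excludes Union. This stands to the extent that one cannot say the trial will ignore Union, only that the stated model does not name it. It does not dispose of the point. The article sets out the restriction in detail and then gives an outcome model that accounts for clustering alone.

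The second reply is that the sample size takes no credit for blocking, so no planned property is lost. That is correct at an ICC of 0.05: power without Union is at least 83.7% in every scenario. Nor do the documents show that Unions differ. All are in one sub-district, and Study area describes rural areas as broadly similar. That says nothing direct about variance, but it gives no support for any particular Union share.

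A reader might also infer three stronger things that the documents do not support:
- **Inflated type I error.** An uncorrected cluster-robust z-test with 33 wards and no Union variance has a simulated size of about 7.4 to 7.7%. The protocol never says it will use that test; a mixed model would fit its wording equally well. Omitting Union by itself is neutral or conservative.
- **A wasted restriction.** Even without Union in the model, blocking balances the arms and reduces the real variance of the contrast, so power rises from 83.7% to 89.3% across the table.
- **An underpowered trial.** Power falls to about 74% without Union (84% with it) only if the total ICC is assumed to be 0.10, half of it between Unions. The protocol plans on 0.05.

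**Conclusion.** The point holds as a mismatch between design and stated analysis: the randomisation is blocked by Union, and the outcome model names clustering by ward but not the block. If Unions differ, the consequence is conservatism. The standard error is overstated by 0 to 31%, the true size lies between 4.9% and 1.3%, and up to about 7 points of power are forgone (89.3% against 96.6%), or about 4 points at a 50% share. If Unions do not differ, leaving Union out does no harm and gains about 1 point.

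These figures rest on a total ICC of 0.05, even attrition of 25%, a two-sided 5% test and an assumed Union share. The validity of the trial and its planned 80% power are not in question under the protocol's own assumptions. The change is still worth making, because it restores the nominal level and uses a restriction that the trial carries out anyway.

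**What to change.** Add one sentence to the analysis section: outcomes will be analysed by a linear mixed model with arm and Union as fixed effects, a random intercept for ward, and Kenward-Roger or Satterthwaite degrees of freedom. An equivalent is an analysis of ward means by arm and Union with 20 residual df. The small-sample degrees of freedom are a safeguard with only 33 wards, since the article does not say how clustering will be handled.

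No data or recruitment change is needed. Union takes 10 degrees of freedom (30 − 20), which costs about 1 point of power (83.7% to 82.4%) if Unions do not differ. If an analysis plan already contains these terms, it is enough to state them alongside the existing sentence.
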